### Prescreening/screening

The long-term follow-up after hematopoietic cell transplant program at COH ensures the active and comprehensive follow-up of all patients who have undergone transplant at COH since 1976 — capturing demographics, disease, and vital status, as well as post-transplant complications such as new malignancies, cardiopulmonary disease, and endocrinopathies. Based on our database, we will prescreen all patients diagnosed with multiple myeloma, who will undergo the transplant at COH. After identifying potentially eligible patients, we will inform their primary hematologist at COH to confirm the physician’s clearance before contacting the eligible patients. Each potentially eligible patient will be contacted by phone to determine the patients’ willingness to participate and to identify patient-reported pre-frailty or frailty. If potentially eligible patients do not respond to our initial contact, we will call up to 3 more times, and discontinue our efforts if there is no response. These individuals will be deemed as non-responders

### Recruitment/randomization

If potentially eligible patients are interested in the study, a trained clinical research assistant will confer with the patients in detail about the additional study inclusion/exclusion criteria by phone. Once patients have been deemed eligible for participation, they will complete an informed consent via a web-based consent form (DocuSign™) prior to performing any further testing (see supplementary file). Participants will be randomly assigned to the telehealth exercise intervention group (*n*=30) or delayed control group (*n*=30). Randomization will be performed following physician’s clearance to participate in exercise and baseline outcome assessment using a computer-generated permuted block randomization. An independent biostatistician will be responsible for randomization and study investigators will be blinded to the randomization. Unblinding may need to occur in the case of a medical emergency or a serious medical adverse event study-directed exercise. Unblinding will be done in consultation with the study physician, and the institutional Data Safety Monitoring Board will be notified according to institutional standard operating procedures.

### Remote measures of physical function and frailty

We will mail gait sensors (for hip, right foot, and left foot), a hand dynamometer, measuring tape, and blue tape to each participant’s home. All of this equipment will be used to assist in measuring physical function and frailty outcomes before and after the intervention at each participant’s home, or remote place of choosing, via live video conferencing. Objective data will be recorded by Bluetooth-enabled sensors into the telehealth exercise platform. All participants will complete an initial 30-min technology support session via Zoom video conferencing, during which research staff will help participants set up their sensors and will verify that the sensors operate properly prior to measuring outcome measures. Frailty will be assessed using a 5-scale frailty index: body mass index, fatigue, level of physical activity, gait speed, and muscular strength. Body mass index will be determined by medical record data while fatigue and level of physical activity will be measured by questionnaires. Gait speed will be collected using gait sensors, and hand dynamometer measurements will be used to assess muscular strength. We will assess physical function remotely using the SPPB under the supervision (through videoconferencing) of study staff. SPPB includes three lower extremity measures completed in the following order: timed balance; gait speed; and chair stand. We will assess timed balance under three conditions: (a) side-by-side stand with both feet placed on the ground for 10 s or when the subject steps out of position; (b) semi-tandem stand with the side of the heel of one foot touching the big toe of the other foot for 10 s or when the subject steps out of position; and (c) tandem stand with the heel of one foot touching the big toe of the other foot for 10 s or when the subject steps out of position. We will assess gait speed by instructing participants to measure and mark a 4-meter flat surface distance, across which they will be asked to walk at their “usual” pace. Next, participants will be asked to walk at their “usual” pace to cover the 4-meter distance once more. Time will be recorded using an electronic timer, and the fastest time will be documented. We will assess chair stand under two conditions — participants will (a) perform a single chair stand and (b) be asked to perform five repeated chair stands as quickly as possible; time to completion will be recorded. All participants will complete the remote physical assessments on week 0, week 9, and week 17.

### Telehealth exercise intervention

The 8-week telehealth exercise intervention will begin for the intervention group after participants have completed the baseline assessments and have been randomized. Exercise equipment (resistance bands, resistance loop bands, and exercise mats) will be directly shipped out to the participants from COH. The exercise trainer will assign the appropriate exercises to the participants via the Moterum platform, which will notify each study participant (via email/text) and provide a Zoom link to start a videoconference meeting 15 min prior to each telehealth intervention. We will provide education on safety precautions during the first remote exercise intervention session (i.e., wearing proper shoes, removing clutter, having enough space to move, having a chair near to take breaks when required, and dealing with dizziness, injuries, or falls). The exercise trainer will ensure proper positioning of the camera and also ensure that the workout environment is safe during each exercise session.

A total of 24 video conferences (at least 30 min/session; 3 days/week for 8 weeks) will take place in each participant’s home or remote place of choosing. Of note, the exercise time of 90min/week represents the minimum time for our intervention, and there is no upper limit. Exercise programs will be individualized and prescribed based on the participant’s baseline assessment, physical limitations, and exercise preferences. The exercise prescriptions will be developed and monitored by a clinical exercise physiologist over the course of the intervention. Each exercise session will consist of exercises targeting four essential components: dynamic balance, strength, core stability, and postural control. If a participant cannot complete the exercises as planned, the exercise trainer will provide alternative options and exercise modifications, as needed, to allow the participant to be successful and reach the desired intensity. Allocated interventions will be discontinued based on the participant’s symptoms. For example, if a participant reports any pain related to a prescribed exercise posture or ratings of perceived exertion >8, other exercise postures will be provided. Furthermore, participants will have the option to reschedule or make up an exercise session if they are unable to attend a workout on the date as planned. Exercise adherence for each participant will be captured on the Moterum platform and extracted to assess the feasibility of the prescribed exercise program.

After completing the 8-week telehealth exercise intervention, participants will be encouraged to continue exercising but will no longer be monitored by the exercise trainer for the next 8 weeks until the follow-up physical assessment (week 17). For participants who have successfully completed their remote physical assessments and questionnaires on Week 0 and who are randomized into the delayed control group, they will be asked to continue maintaining their current lifestyle for 17 weeks. On weeks 9 and 17, participants will complete the remote physical assessment and questionnaires again. The study staff will check in with the participants before week 17 and ask them if they would like to participate in the telehealth exercise intervention or not. The exercise program will be offered to the participants as a courtesy and is not mandatory to complete study procedures. All appropriate exercise equipment will be shipped out accordingly to those who would like to participate in the 8-week telehealth exercise program, and outcome measures will not be collected once the program is completed. The study will end after the week 17 assessment for participants in the delayed control group who do not want to participate further with the telehealth exercise option.

### Questionnaires (weeks 0, 9, and 17)

Additional patient-reported outcomes to be measured include instruments that have been found to be reliable, valid, responsive, brief, and easy to administer in cancer patients. All questionnaires will be sent out to the participants electronically via Moterum, and all questionnaires will be self-administered by the patient unless assistance is requested for filling them out. If assistance is preferred, study staff will help over the phone. However, the ability to complete the questionnaires does not influence eligibility criteria.

We will use International Physical Activity Questionnaire, Short Form (IPAQ-SF) to estimate participants’ perception of participating physical activity. That said, we acknowledge that the IPAQ-SF may not detect small changes in levels of physical activity. This questionnaire provides common instruments that can be used to obtain internationally comparable data on health-related physical activity in young and middle-aged adults.

*Quality of life* will be assessed using the Functional Assessment of Cancer Therapy – Multiple Myeloma (FACT-MM) scale developed for the assessment of patient symptoms and Quality of Life in multiple myeloma patients.

*Fatigue* will be assessed using the 13-item FACIT-fatigue scale for the assessment of fatigue/tiredness and its impact on daily activities and functioning in cancer patients.

*Pain* will be assessed by the 15-item Brief Pain Inventory. This self-administered questionnaire measures both the intensity of pain (sensory dimension) and the interference of pain in the patient’s life (reactive dimension). It also asks about pain relief, pain quality, and patient perception of the cause of pain.

*Sleep quality* will be assessed by the Pittsburgh Sleep Quality Index. This is a self-rated questionnaire which assesses sleep quality and disturbances over a 1-month time interval. It looks at subjective sleep quality, sleep latency, sleep duration, habitual sleep efficiency, sleep disturbances, use of sleeping medication, and daytime dysfunction.

### Power calculations

This study is powered to detect a difference in physical function between the two groups after the 8-week intervention. Assuming that a type 1 error = 0.05, data is collected at two time points, there is 20% attrition from baseline to week 9, and there is a correlation of ≥ 0.8 for within-person measurements between time, 60 patients (30 per group) at baseline will achieve 80% power to detect an effect size of at least 0.40 at week 9. A previous study of an 8-week exercise intervention in cancer survivors showed that baseline physical function was 6.7, SD=2.7, with a correlation of 0.9 between baseline and post-intervention [28]. By applying these values to patients with multiple myeloma who underwent HSCT, the present study will be able to show a difference of at least 1 in function score between the treatment groups post-intervention. A 1-unit decrease in the physical function score has been associated with a 12% increase in all-cause mortality in cancer survivors [29], and represents a clinically meaningful difference. The attrition rate in our previous study was 0% [28]. Nevertheless, we conservatively assumed a higher attrition rate of 20% and a lower correlation of 0.70; thus, 60 subjects at baseline (30 telehealth exercise intervention, 30 delayed controls) should provide even greater power since our preliminary study had a higher correlation as well as an attrition of less than 10%.

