## Methods/design

A single-center, investigator-blinded randomized, parallel-group, superiority study was conducted to demonstrate the efficacy of a telehealth exercise intervention on physical function and frailty in patients with multiple myeloma who received HSCT at City of Hope (COH). Figure 1 depicts the flow of the study. We will conduct an 8-week telehealth intervention that will include baseline (week 0) and post-intervention measures (week 9, week 17) on physical function and frailty measures. We will randomize 60 pre-frail or frail patients with multiple myeloma (1:1) to either the 8-week telehealth exercise intervention group (*n*=30) or the delayed control group (*n*=30). All study procedures, including screening and enrollment, will be performed using a telehealth-based approach and will not require participants to be assessed at a clinical center.

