### Statistical analysis

We will generate descriptive statistics for participants’ demographics, lifestyle behaviors (physical activity, tobacco use), family history of chronic disease, history of other comorbidities (e.g., hypertension, diabetes, dyslipidemia, thyroid disease), and cancer treatment-related exposures. We will assess participation bias by comparing demographics (age, gender, race/ethnicity) and treatment-related exposures among participants and non-participants. Although the number of adverse events is not the major outcome of the study, we will report any adverse events during the study intervention period. We will use a two-sided type I error=0.05. An intention-to-treat analysis will be done by including all randomized participants. We will also conduct another analysis by excluding participants that demonstrate <70% compliance rates within the telehealth exercise sessions completed (17/24). *Hypothesis 1*: The intervention will improve the SPPB test, as objectively measured using Bluetooth-enabled biosensors. We will assess changes in physical function from baseline to week 9 by using the Generalized Estimation Equation (GEE) model with an indicator variable of time, accounting for within-person correlations in measurements. Treatment by time interaction will be included in GEE and its significance tested to assess treatment effects. Body mass index, age, and race will be determined through medical records and included in GEE as a priori covariates for adjustment. Changes in physical function measures from baseline to week 9 will also be examined by a paired *t*-test (within the treatment group). A 2-sided significance level of *p*<0.05 will be used. *Hypothesis 2*: The intervention will improve a 5-scale frailty index, as measured by patient-reported questionnaires. We will assess group differences in changes in the proportion of participants who are of pre-frail or frail from baseline to week 9 using the GEE approach for proportions, accounting for correlation between measurements. As in hypothesis 1, we will include the same covariates for adjustment in the analysis. *Hypothesis 3*: Intervention-related improvements in physical function and frailty will be sustained at week 17. We will examine the long-term effects of the telehealth exercise intervention by fitting GEE models for the outcomes at weeks 9 and 17. The model will include the treatment main effect (to allow for group differences at week 17), time, and the treatment group by time interaction. Contrasts will be used to test if the group difference at week 17 equals that at week 9. As in hypothesis 1, we will include the same covariates for adjustment. Additionally, between-group differences in outcome values at week 17 will be computed, along with 95% confidence intervals, and compared to the differences at week 9. Linear mixed-effects modeling will be used to evaluate the effect of interventions over time on the primary and key secondary outcomes. The models incorporate subject-specific random effects to account for within-subject correlation due to repeated measures. Group averages, as well as subject-specific intercepts and slopes, will be estimated to capture potential variations in the baseline values and slopes among individuals. Linear mixed-effects models accommodate missing data due to dropout, such that all randomized participants can be included. We will compare participants who complete the study with those who do not and identify potential factors that are associated with dropout. An interim analysis is not currently planned for this study.

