Although this study will provide the first evidence of a novel telehealth exercise approach targeting frailty and physical function in patients with multiple myeloma, it is beyond the scope of the current study to elucidate the mechanisms of improving frailty with exercise. Our study has the potential to demonstrate that frailty is maintained and not worsened during the intervention when compared to the delayed control group, which will be a clinically important finding. We recognize that poor retention is a possibility, given the time and effort needed to partake in an intervention study. Therefore, we have accounted for a 20% attrition rate (from randomization to week 17 post-intervention). This takes into consideration patient death, recurrence of cancer, illness, or loss to follow-up. We acknowledge that there may be differential loss to follow-up according to participant attributes and prognosis, which may contribute to participation bias and/or survival bias. To minimize participation bias, we will incorporate many of the strategies (e.g., reminders, incentives) that we have successfully used to maintain excellent participation rates in our exercise intervention studies to date. Attrition will be monitored in real time, allowing us to address obstacles in a timely manner. Differential loss to follow-up due to prognosis, death, and missing data will be addressed using statistical methods of pattern mixture models and multiple imputation. Finally, recruitment of patients with multiple myeloma can be challenging. However, our ongoing successful recruitment strategies in place for the current study, which includes collaborating with the hematology team at COH, appear to be a successful recruitment plan.

This study will provide critical evidence that contributes to the development of comprehensive telehealth exercise programs in HSCT survivors by investigating the effects of an 8-week telehealth exercise intervention in HSCT survivors with the potential of demonstrating improvements and sustainability in physical function. If successful, our approach would be low cost, easily disseminated, and have potential implications for the management and prevention of frailty in HSCT survivors as well as other cancer survivors at risk of developing frailty after cancer treatment.

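### The stated 80% power for an effect size of 0.40 does not follow at the assumed correlation of 0.8 (57%) or at 0.70 (42%); it needs about 0.88, and the 1-point claim needs about 0.9

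*Protocol article*

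**What the plan says.** All the inputs are in the protocol article.

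- **Power claim** (Power calculations): "60 patients (30 per group) at baseline will achieve 80% power to detect an effect size of at least 0.40 at week 9". The conditions attached are "Assuming that a type 1 error = 0.05, data is collected at two time points", 20% attrition from baseline to week 9, and "there is a correlation of ≥ 0.8 for within-person measurements between time".
- **Raw-scale claim** (same paragraph): the section takes an SD of 2.7 and a baseline-to-post correlation of 0.9 from a previous study in cancer survivors. It applies these to the trial population and concludes that "the present study will be able to show a difference of at least 1 in function score" between the groups.
- **Claim of caution** (end of the paragraph): "we conservatively assumed a higher attrition rate of 20% and a lower correlation of 0.70". It adds that 60 subjects should give still more power, because the preliminary study had a higher correlation and less attrition.
- **Test** (Statistical analysis): "We will use a two-sided type I error=0.05". The treatment effect on physical function is tested through the treatment-by-time interaction in a GEE model of change from baseline to week 9.

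**The concern.** One paragraph gives two design values for the same correlation: at least 0.8, then 0.70. A third value, 0.9, is the empirical one behind the 1-point statement. With two time points, power for a treatment-by-time test depends heavily on this correlation, so the three values cannot share one power figure.

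This paragraph is the only justification given for 60 patients, and it concerns the primary endpoint. It calls 1 point clinically meaningful and tells the reader that the sample size was set cautiously. A reader who believes that will take a null result as fair evidence against a 1-point effect. If the true correlation is 0.8 or 0.70, the trial would miss such an effect about half the time or more.

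**Working it through.** **Inputs.** 30 per arm, 20% attrition, so 30 × 0.8 = 24 completers per arm and 46 degrees of freedom. Two-sided alpha 0.05. Effect 0.40 in SD units of the outcome. SD 2.7. Correlation ρ = 0.70, 0.8 or 0.9. Equal SDs at both visits are assumed.

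**Formulas.** The SD of the compared quantity, as a multiple of the outcome SD, is:

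- treatment-by-time (change): √(2(1 − ρ));
- baseline-adjusted: √(1 − ρ²), shown as a more favourable alternative.

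The noncentrality is effect / (SD × √(2/24)), and power comes from the noncentral t distribution.

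**The plan's 80% for 0.40.** At ρ = 0.8 the change SD is √0.4 = 0.632. The noncentrality is 0.40 / (0.632 × 0.2887) = 2.19, which gives 57% power. At ρ = 0.70 the change SD is √0.6 = 0.775, the noncentrality is 1.79 and power is 42%.

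| ρ | Power for 0.40 SD, change / adjusted | Power for 1 point (1/2.7 = 0.37 SD), change / adjusted | Difference detectable at 80%, change |
|---|---|---|---|
| 0.70 | 42% / 48% | 37% / 42% | 0.64 SD = 1.73 points |
| 0.8 | 57% / 62% | 51% / 55% | 0.52 SD = 1.41 points |
| 0.9 | 86% / 87.5% | 80% / 82% | 0.37 SD = 1.00 point |

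The last column uses a standardised detectable difference of 0.826 at 80% power with 24 per arm. At ρ = 0.8, for example, 0.826 × 0.632 = 0.522 SD, and 0.522 × 2.7 = 1.41 points.

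**Correlation needed.** 80% power for 0.40 requires a change SD of 0.40 / 0.826 = 0.484. So 2(1 − ρ) = 0.234 and ρ = 0.88 (0.87–0.88 if baseline-adjusted). For 1 point, ρ must be about 0.90 (0.89 if adjusted).

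**Completers needed for 0.40.** At ρ = 0.8, 41 per arm (37 if adjusted). At ρ = 0.70, 60 per arm (52 if adjusted). The plan expects 24.

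**Other readings tried.**

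- *No attrition (30 per arm), ρ = 0.8:* 67% / 72%.
- *All 30 baselines and 24 follow-ups per arm in the interaction test.* The variance per arm is (1 − ρ²)/24 + (1 − ρ)²/30. Power by the normal approximation is 60% at 0.8 and 44% at 0.70.
- *Week-9 values alone, 24 per arm:* 27%.
- *One-sided with no attrition, ρ = 0.8:* 78% / 82%. This drops both the two-sided test and the attrition that the plan states.
- *0.40 read as Cohen's f (a difference of 0.8 SD) on the average of the two visits:* 82% at ρ = 0.8. This is not the interaction test. It implies 0.8 × 2.7 = 2.16 points rather than about 1. Power on this reading also falls as ρ rises (84% at 0.70, 79% at 0.9), the reverse of what the paragraph says.

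No reading that keeps all the stated inputs gives 80%.

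**The case against.** The strongest reply is that the 1-point sentence is right as written. It is tied explicitly to the previous study's SD of 2.7 and correlation of 0.9. On those values, power for 1 point is 80–82% even after 20% attrition. That stands. A reader might infer from the table that the trial cannot reliably detect 1 point, but the document does not support so flat a conclusion, because the answer depends on which correlation holds. Nor can the 42–62% range be used to argue it: those are powers for 0.40 SD, which is 0.40 × 2.7 = 1.08 points.

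Second, the stated correlation is a lower bound, and the 80% is reached over part of its range, from about 0.88 upward. This is true, but a claim made for every value of at least 0.8 must hold at 0.8. There it falls short by about 20 percentage points.

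Third, adjustment for body mass index, age and race might add precision. The document gives no figure for this. To restore 80%, the covariates would have to explain 1 − 0.234/0.40 = 41% of the variance of change at ρ = 0.8, or 1 − 0.234/0.60 = 61% at 0.70. The document offers no basis for either.

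Fourth, it is correct that a higher correlation and lower attrition than assumed would raise power. What fails is the starting point, since 0.70 with 20% attrition is well below 80% to begin with.

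A reader might also add that the same 20% attrition runs to week 9 in the power section and to week 17 in the Discussion. This is a wording mismatch that changes no number here: both leave 24 per arm.

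**Conclusion.** The 80% power figure for an effect size of 0.40 is wrong at the paragraph's own lower bound of 0.8 (57% for the planned test, 62% if baseline-adjusted). It is further off at the value described as conservative, 0.70 (42% / 48%). The paragraph names two incompatible design correlations. Its 1-point statement holds at 0.9, with nothing to spare: 80–82%, against 51–55% at 0.8 and 37–42% at 0.70. The implication that 0.70 already supports 60 patients is therefore false.

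The conclusion is about the stated power. The document does not show that the trial is unable to detect 1 point, and the error does not affect the primary estimate, its test or the type I error.

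The assumptions are that 0.40 is a difference in outcome SD units, which fits the 1-point and SD 2.7 scaling; that SDs are equal at both visits; that 24 completers remain per arm; and that covariates bring no gain in precision.

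**What to change.** Keep 60 patients and rewrite the power section around one design correlation. Suitable content, for 24 completers per arm, two-sided 0.05, the change analysis and SD 2.7:

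- 80% power for 0.52 SD (1.4 points) if the correlation is 0.8;
- 80% power for 0.64 SD (1.7 points) if it is 0.70;
- 80% power for 1.0 point only if it is about 0.9, as in the previous study.

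Delete or correct the sentence that presents 0.70 as a conservative assumption with power in reserve.

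The cost is a change of wording. No patients, visits or analyses are added. The drawback is that the published figure becomes less favourable, and the 1-point target is seen to rest on a correlation carried over from a previous study in cancer survivors.
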